## Abstract

**Background:**

The present study protocol describes the trial design of a clinician training intervention to improve physical activity counseling in underserved primary care settings using the 5As. The 5As (Ask, Advise, Agree, Assist, Arrange) are a clinical tool recommended for health behavior counseling in primary care.

**Methods/Design:**

The study is a two-arm randomized pilot pragmatic trial to examine a primary care clinician communication intervention on use of the 5As in discussion of physical activity in audio-recorded office visits in an ethnically diverse, low-income patient population. The study setting consists of two federally qualified community health centers in Rochester, NY. Eligible clinicians (n=15) are recruited and randomized into two groups. Group 1 clinicians participate in the training intervention first; Group 2 clinicians receive the intervention six months later. The intervention and its outcomes are informed by self-determination theory and principles of patient-centered communication. Assessment of outcomes is blinded. The primary outcome will be the frequency and quality of 5As discussions as judged by evaluating 375 audio-recorded patient visits distributed over baseline and in the post-intervention period (immediately post and at six months). Secondary outcomes will be changes in patients’ perceived competence to increase physical activity (Aim 2) and patients and clinicians beliefs regarding whether pertinent barriers to promoting exercise have been reduced. (Aim 3). Exploratory outcomes (Aim 4) are potential mediators of the intervention’s effect and whether the intervention affects actual enrollment in the community program recommended for exercise. The analysis will use repeated measures (in the form of recorded office visits) from each clinician at each time point and aggregate measures of Groups 1 and 2 over time.

**Discussion:**

Results will help elucidate the role of 5As communication training for clinicians on counseling for physical activity counseling in primary care. Results will explore the effectiveness of the 5As model linked to community resources for physical activity promotion for underserved groups.

## Background

With rapid increases in overweight, obesity, and related chronic conditions in the US and globally, [1,2] primary care faces an ongoing challenge and opportunity to translate promising physical activity interventions into practice [3]. Current US recommendations for healthy adults aged 18–65 entail either moderate-intensity aerobic physical activity for a minimum of 30 minutes/day for five days per week, vigorous intensity activity for a minimum of 20 minutes/day for three or more days per week, or a combination [4]. The World Health organization recommends that primary care be a cornerstone for physical activity promotion [5]. Primary care represents an important avenue for physical activity promotion in the US because about 11% of the population visits primary care physicians every month, 80% of adults visit a physician within a one-year period, [6] and more than 40% of adults over age 40 have had the same doctor for over 5 years [7].

Effective physical activity counseling in primary care is hampered by limited time and competing demands [8,9]. Primary care physicians spend a mean of 47 seconds in health maintenance and chronic care visits– though the time varies widely- providing combined diet and exercise advice to patients [10]. Not surprisingly, less than half of patients receiving such advice were able to recall it. Yet, spending even an extra minute in the visit discussing exercise can more than double patient recall [11].

Limited evidence suggests brief clinician counseling improves short- and long-term physical activity outcomes [12,13]. Specifically, clinician counseling as brief as one or two 3 to 5 minute sessions result in a significant increase in patients’ physical activity levels at eight months [13]. The 5A guidelines, in which clinicians Ask about (or Assess), Advise about, Agree upon, Assist and Arrange follow-up regarding patients’ behavior change efforts[14,15]—is a framework for brief counseling that may promote physical activity. Additionally, patient centered communication (PCC) -- in which clinicians elicit patients’ social contexts, values, expectations, and beliefs relevant to the target behavior, and support patient choice in whether, when and how to engage in physical activity—may also promote behavior change by patient participation, satisfaction, trust, and adherence to treatment plans [16-18]. Understanding each patient’s unique perspective, context and wishes is particularly salient for underserved populations whose socio-cultural contexts may differ substantially from those of their clinicians [19]. In the absence of patient input, clinicians may not fully appreciate the facilitators and barriers to physical activity that patients from diverse background confront.

Despite the potential impact, relatively little research has investigated how to promote effective physical activity counseling in primary care using the 5As or PCC, particularly for underserved patients. For underserved populations, counseling linked to accessible community-based resources may be a promising strategy.

### Conceptual framework

A challenge in applying health behavior research to clinical care is the existence of multiple overlapping theories of communication and behavior change. This project contains three common elements – motivation, skills, and support- in its design and measurement. Patients undertake behavior change when they experience internal motivation rather than external control, social support to change behavior, and the perceived competence with instrumental skills to accomplish the change and address barriers.

One theory that unifies these three elements is self-determination theory [20]. SDT is a general theory of human motivation, with the foundation that humans are innately motivated for personal growth and health. According to SDT, individuals have needs for autonomy, competence (e.g., feeling able to achieve a desired outcome), and relatedness to others [17]. Autonomy is defined as the need to have choice and volition in one’s behavior. Competence

Is defined as the need to feel optimally challenged and capable of achieving outcomes. Autonomy support has been linked to stronger intentions to be physically active, Rouse [21] long-term retention, higher levels of perceived autonomy for physical activity, initiation and maintenance of physical activity, greater weight loss in weight loss programs, [17,22] and perceived competence for physical activity [23]. A recent meta-analysis of 30 studies found a significant positive correlation between autonomy support and physical activity, with positive effect sizes in the small to moderate range for physical (0.08 to 0.39) and mental (0.22 to 0.37) health [24].

Additional information about self-determination theory and its application to the design of the intervention and choice of measures is in (sections Description of intervention and Evaluation and measures).

While self-determination theory is the over-arching theory used in this project, there are two other components incorporated into the conceptual framework. First, the 5A guidelines (“5As”) [14] focus on clinician completion of five specific tasks necessary to effectively counsel patients about health habits. Originally developed by the National Cancer Institute as the “4As” for smoking cessation, [14] the 5As have been endorsed by the US Preventive Services Task Force, [15] the Canadian Task Force on Preventive Care, [25] and national guidelines in the UK [26] and Sweden [27] as a unifying framework for behavioral counseling in primary care for non-tobacco health behaviors [7,15,28-30]. The 5As are a framework for clinicians to ASK about current behavior, ADVISE a change, ASSESS willingness to change and willingness to enroll in a community program supporting physical activity, ASSIST with goal-setting and ARRANGE follow-up. ASK is important for behavior change to explicitly identify physical activity as potentially in need of change; one’s physical activity level is usually unknown without specifically asking and rarely the main reason for seeking clinical care. ADVISE [15] is important for health behavior change by specifically linking physical activity recommendations to a person’s own health concerns or life context, in order to maximize motivation for change [31]. ASSESS promotes behavior change by the patient and clinician coming to common ground and collaborating on physical activity goals and strategies. ASSIST [15] is relevant for behavior change by offering additional resources, referral options, or practical problem-solving strategies help the patient secure the necessary support for physical activity change [15,32]. Finally, ARRANGE is important for behavior change by providing the opportunity to follow-up and re-evaluate one’s behavior change efforts and perhaps adjust the change plan [15].

The 5As have been endorsed as a unifying framework for behavioral counseling in primary care [7,15,28-30]. The 5As have been shown to increase healthy behaviors, positively influence mediators of behavioral change, and increase clinician communication skills about health behavior change [13,15,28-30,33-35]. The 5As are incorporated into the clinician training intervention’s design and measurement.

The second component in the conceptual framework is patient-centered communication (PCC) [36,37]. Patient-centered communication directly addresses barriers in counseling for underserved populations that may not be adequately captured in the 5As alone. Understanding patients’ social context might help narrow the gap in the social distance between patient and physician. For example, miscommunication can occur if clinicians give advice without understanding the patient’s life situation, without encouraging the patient to ask questions and take an active role, and without reinforcing the patient’s learning during the office visit by summarizing, checking, and verifying mutual understanding [38]. PCC improves trust, [16] motivation, adherence and control of some chronic illness [17,18] however its application to physical activity counseling is less well understood. PCC consists of several constructs; [39-44] for this project, we focus on the constructs overlapping with SDT of (1) autonomy support, defined as activating and involving patients in choices about their care [45] such that they feel supported and empowered, [46] and (2) understanding patients’ social context.

Table 1 summarizes how self-determination theory, the 5As, and patient-centered communication inter-relate in the project. In the intervention’s design, interactive group and peer discussions are incorporated into the training techniques to increase both clinician and patient motivation for physical activity discussion. This training technique relates to the 5As and PCC by increasing clinician motivation to ASK, ADVISE, and ASSESS their patient’s physical activity via the use of patient-centered communication skills of supportive listening and open-ended questions. The intervention is designed to provide a choice of options and community resources for clinician to ASSIST and ARRANGE referral for physical activity, thus aiming to increase clinician autonomy supportiveness and competence to counsel. In the assessment and measurement, SDT, the 5As and PCC inter-relate in the analysis of the discussions via ratings of the content of the physical activity discussions (using the 5As), and the quality of the physical activity discussions (whether they were autonomy supportive-SDT, and whether they explored the clinician made supportive statements, and verified understanding and agreement-PCC).

**Table 1 T1:** Summary of intervention components and corresponding conceptual framework

	**Self-determination theory**	**5As**	**Patient-centered communication (PCC)**
Design of intervention (key concepts)	· Promoting autonomy supportive skills for clinicians when counseling patients about physical activity	· Use of 5As for physical activity counseling	· Understanding patients’ social context
			· Offering support
			· Encouraging patient participation
	· Increasing clinician perceived competence to counsel		
Intervention training (curriculum components)	· Interactive discussion on strategies to increase both patient motivation for physical activity and clinician motivation to raise the topic	· Introduction, repetition, and reinforcement of each of the 5As via didactic presentation, role play, and standardized patient feedback	· Role play and group discussion to develop and reinforce supportive listening and open-ended questions about physical activity
	· Offering a choice of community resources for referral		
	· Offering a choice of optional electronic health records tools and eliciting ongoing feedback		
			· Use of standardized patients to give feedback to clinicians on PCC skills
Assessment/measurement (clinician perspective)	Clinician surveys and interviews	Clinician interviews asking about recall of 5As	Clinician surveys and interviews
Assessment/measurement (patient perspective)	Patient ratings of autonomy support of clinicians, perceived competence for physical activity	Patient report of 5As discussions of physical activity	Patient ratings of trust and satisfaction with their relationship with their clinician; patient interviews on communication skills of their clinicians
Assessment/measurement (blinded coder)	Coding of autonomy supportiveness (global rating and for each A)	Coding of content and quality ratings for the 5As	Coding of supportive statements, exploration of patient’s social context related to physical activity, encouraging questions, verifying understanding and agreement

The purpose of this paper is to describe a study protocol of a clinician training intervention to improve physical activity counseling in underserved primary care settings using the 5As. Aim 1 of the project assesses whether a 5As physical activity communication training intervention increases communication skills during visits underserved patients in the post-intervention period (immediately post and at one year compared to baseline). Aim 2 assesses whether the 5As communication training intervention improves patients’ perceived competence for physical activity. Aim 3 assesses whether the 5As communication training intervention improves clinicians’ autonomy support for physical activity with their patients. Aim 4 assesses whether clinicians and patients perceive the 5As counseling to be feasible and sustainable and whether the communication training addresses pertinent barriers to promoting physical activity.

The hypotheses are as follows:

H1: Clinicians who complete the communication intervention will increase their use of all 5As for visits in which the topic of physical activity is raised as judged by comparing the audio-recordings of office visits in the post-intervention period (immediately post and at one year) compared to baseline.

H2: The intervention will increase clinician autonomy supportiveness when counseling about physical activity.

H3: The intervention will increase patient perceived competence for adopting physical activity.

H4: Specific patient recall of the Assist and Arrange will be associated with the greatest patient perceived competence to adopt physical activity compared to recall of Ask, Advise, or Assess.

### Conceptual framework

A challenge in applying health behavior research to clinical care is the existence of multiple overlapping theories of communication and behavior change. This project contains three common elements – motivation, skills, and support- in its design and measurement. Patients undertake behavior change when they experience internal motivation rather than external control, social support to change behavior, and the perceived competence with instrumental skills to accomplish the change and address barriers. One theory that unifies these three elements is self-determination theory [20]. We use self-determination theory in the design of the intervention and choice of measures (described further in sections 2.11 and 2.14).

While self-determination theory is the over-arching theory used in this project, there are two other components incorporated into the conceptual framework. First, the 5A guidelines (“5As”) [14] focus on clinician completion of five specific tasks necessary to effectively counsel patients about health habits. Originally developed by the National Cancer Institute as the “4As” for smoking cessation, [14] the 5As have been endorsed by the US Preventive Services Task Force, [15] the Canadian Task Force on Preventive Care, [25] and national guidelines in the UK [26] and Sweden [27] as a unifying framework for behavioral counseling in primary care for non-tobacco health behaviors [7,15,28-30]. The 5As are a framework for clinicians to ASK about current behavior, ADVISE a change, ASSESS willingness to change and willingness to enroll in a community program supporting physical activity, ASSIST with goal-setting and ARRANGE follow-up. The 5As have been endorsed as a unifying framework for behavioral counseling in primary care.[7,15,28-30] The 5As have been shown to increase healthy behaviors, positively influence mediators of behavioral change, and increase clinician communication skills about health behavior change [13,15,28-30,33-35]. The 5As are incorporated into the clinician training intervention’s design and measurement.

The second component in the conceptual framework is patient-centered communication (PCC) [36,37]. Patient-centered communication directly addresses barriers in counseling for underserved populations that may not be adequately captured in the 5As alone. Understanding patients’ social context might help narrow the gap in the social distance between patient and physician. For example, miscommunication can occur if clinicians give advice without understanding the patient’s life situation, without encouraging the patient to ask questions and take an active role, and without reinforcing the patient’s learning during the office visit by summarizing, checking, and verifying mutual understanding [38]. PCC improves trust,[16] motivation, adherence and control of some chronic illness [17,18] however its application to physical activity counseling is less well understood. PCC consists of several constructs; [39-44] for this project, we focus on the constructs overlapping with SDT of (1) autonomy support, defined as activating and involving patients in choices about their care [45] such that they feel supported and empowered, [46] and (2) understanding patients’ social context.

Table 1 summarizes the application of self-determination theory, the 5As, and patient-centered communication in the project.

## Methods

### Study design

The study methods described herein have been developed and informed by the CONSORT criteria and by other work in the field [12,13,47-49] Figure 1. 

**Figure 1 F1:**
[figure not shown]
Study Schema.

The project is a two-arm randomized pragmatic trial to pilot a communication training intervention for primary care clinicians (n=13) on use of the 5As to promote physical activity in underserved patients. The intention of training focuses on clinicians to communicate effectively using the 5As and patient-centered communication skills firmly linked to a theory of human motivation (Aim 1). Clinicians are randomly assigned to two groups. Group 1 participates in the training intervention first; Group 2 receives the intervention six months later. The primary outcome is the frequency and quality of clinician use of the 5As during routine office visits, post-intervention compared to baseline. Secondary outcomes and potential mediators are changes in patients’ perceived competence to adopt physical activity (Aim 2) and clinician autonomy support of physical activity with their patients (Aim 3). Given the myriad of barriers reported in the literature, another secondary outcome is whether clinicians believe that the intervention addresses pertinent barriers to promoting exercise (Aim 4). Exploratory outcomes are other potential mediators of the intervention’s effect and the effect of the intervention on actual physical activity levels in a subset of participants. The schema shows the overall study design and timeline.

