### Sample size and power

The primary goal of this study is to evaluate the influence of a clinician communication intervention on use of the 5As in communication about physical activity in the post-intervention period (immediately post and at one year) compared to baseline as assessed by audio-recorded data. The sample includes a planned maximum of 15 clinicians (eight in Group 1 and seven in Group 2) measured at three (Group 1) or four (Group 2) time points. The measurements consist of a total of 25 audio-recorded patient visits from each clinician distributed across each of the evaluation points: approximately 10 recordings at baseline and seven or eight each at post- and follow-up points. Of the planned 375 recorded visits, we estimate up to 20% may be excluded from the analysis due to the patient or clinician shutting off the recorder, or equipment malfunction, thus leaving approximately 300 recorded visits (about seven per clinician per time point, or 20 total per clinician) for analysis. Pilot data with 46 recorded visits from eleven physicians showed that the average 5A score was 0.74, with a standard deviation of 1.06. Thus, with 15 clinicians and 20 patients per clinician, we will have 80% power to detect a difference of 0.54 between Groups 1 and 2, using a two-sided t-test at 0.05 significance level.

The final analyses will use a mixed effects model to incorporate correlations between the observations made by the same physician. The variance in 5A scores taken from patients within a single physician's patient panel will likely be smaller than the variance of scores taken from patients between different physicians, i.e. the intraclass correlation coefficient (the ratio of between-physician variance to the sum of between- and within-physician variances) will be larger than zero. We have conducted a series of power analyses taking this clustering into effect using a Mann–Whitney two-sample t-test of means.

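### The number of randomised clinicians is 13 in the study design section but 15 in the abstract and, as a maximum, in the power section; the visit totals and the power statement are built on 15 only

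*Protocol article*

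**What the plan says.** The protocol article gives the number of clinicians in three places.

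- Abstract, Methods/Design: "Eligible clinicians (n=15) are recruited and randomized into two groups".
- Methods, Study design (text under Figure 1): the training is piloted in "primary care clinicians (n=13) on use of the 5As to promote physical activity in underserved patients".
- Sample size and power: "a planned maximum of 15 clinicians (eight in Group 1 and seven in Group 2".

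The visit totals appear in the abstract, "evaluating 375 audio-recorded patient visits distributed over baseline and in the post-intervention period", and in the sample size section. The latter plans "a total of 25 audio-recorded patient visits from each clinician" and continues: "Of the planned 375 recorded visits, we estimate up to 20% may be excluded from the analysis", "thus leaving approximately 300 recorded visits (about seven per clinician per time point, or 20 total per clinician) for analysis". It then claims 80% power for a difference of 0.54 between the groups, with a pilot standard deviation of 1.06 and a two-sided t-test at the 0.05 level, for 15 clinicians with 20 patients each. It says that the ICC exceeds zero and that power analyses allowing for clustering were done, but it reports no ICC.

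**The concern.** Clinicians are randomised and visits are nested within them, so the number of clinicians governs both the amount of data and the precision of the comparison between groups. The article prints two different numbers in current text and does not label 13 as enrolled, expected or minimum. A reader cannot tell how many clinicians the trial plans to randomise, or against which target recruitment should be judged. If the number is 13, the printed visit totals are wrong and the power statement describes a larger trial than the one planned. If 15 is only a ceiling, the power statement is a best case and nothing is said about a shortfall of two.

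**Working it through.** **Inputs from the article.** 25 visits per clinician; up to 20% lost; 20 analysable visits per clinician; SD 1.06; difference 0.54; two-sided 0.05; 8 and 7 clinicians per group. **Assumptions, not in the article:** a 7:6 split for 13 clinicians, and every ICC value below.

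**1. Visit totals.** Planned visits = clinicians × 25; analysable visits = planned × 0.80.

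- 15 clinicians: 15 × 25 = 375; 375 × 0.80 = 300. Both printed figures are reproduced.
- 13 clinicians: 13 × 25 = 325; 325 × 0.80 = 260.

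The totals therefore fit 15 only. This step needs no assumption.

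**2. The stated power, from the stated inputs.** With visits taken as independent, the standard error is SE = 1.06 × √(1/n₁ + 1/n₂).

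- 15 clinicians, 160 and 140 visits: SE = 0.123, 0.54/SE = 4.40, power 99.2%. The difference detectable with 80% power is 0.34.
- 13 clinicians, 140 and 120 visits: SE = 0.132, 0.54/SE = 4.10, power 98.3%. The detectable difference is 0.37.

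So the printed pair of 80% and 0.54 does not follow from the plain t-test on 300 visits at either size. It must contain something that the article does not state.

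**3. Readings that bring 15 clinicians to about 80%.** For clustering, multiply the variance by the design effect 1 + (20 − 1) × ICC.

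| Reading | Power for 0.54, 15 clinicians (8:7) | Power for 0.54, 13 clinicians (7:6) | Detectable difference, 13 clinicians |
|---|---|---|---|
| t-test on clinician means, 20 visits each, ICC 0.058 (design effect 2.11; df 13 and 11) | 80% | 72.8% | 0.59 |
| Design effect with visit-level df, 20 visits each, ICC 0.077 (design effect about 2.45) | 80% | 74.0% | 0.58 |
| No clustering, 8 visits per clinician at one time point (64 v 56; 56 v 48) | 78.9% | 72.8% | 0.59 |

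The two ICCs were solved for so as to return 80% at 15 clinicians; they are not the authors' values. For the third row, the normal approximation gives 79.5% and 73.6%, with a detectable difference of 0.58.

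**4. Range over assumed ICCs.** t-test on clinician means, 20 visits each, difference 0.54:

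| Assumed ICC | 15 clinicians | 13 clinicians |
|---|---|---|
| 0.02 | 93% | 89% |
| 0.04 | 87% | 80% |
| 0.05 | 83% | 76% |
| 0.10 | 67% | 59% |
| 0.20 | 46% | 40% |

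In this model 13 clinicians keep 80% power up to an ICC of about 0.04.

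**The case against.** The strongest defence is the word maximum in the sample size section: a trial with a ceiling of 15 may have 13, so those two passages are not strictly incompatible. The trial is also a pilot, no calculation uses 13, and the sample size section is consistent with itself on the number of clinicians. On this view the matter is one of labelling.

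Part of this stands. The flat conflict is between the abstract and the study design section, and 13 may simply be the number enrolled. But the article does not say so, the abstract states 15 without a qualifier, and no power is given for fewer than 15.

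A reader might go further and infer that the 80% power holds at 15 clinicians and is lost at 13. The document does not support that as an unconditional statement. On its printed inputs without clustering, power is about 99% at 15 and 98% at 13, so 80% is reproduced at neither. The fall to about 73% rests on a back-solved ICC, or on a one-time-point reading, and on an assumed 7:6 split. At an ICC of 0.04 or below, 13 clinicians still reach 80%.

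**Conclusion.** The point holds for the number of clinicians and for the visit totals. The article gives 13, 15 and at most 15 for the randomised unit without explanation, and 375 and 300 visits are right only for 15; for 13 they are 325 and 260, a difference of 50 planned and 40 analysable visits. This part is certain.

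The loss of power is conditional. If 0.54 already allows for an ICC of about 0.06 to 0.08 with 20 visits per clinician, or for about 8 visits per clinician at one time point, then 13 clinicians split 7:6 give about 73–74% power, 5 to 7 percentage points below the same reading at 15. Without the authors' ICC the size of the loss cannot be fixed. At every ICC in the range shown, 13 gives less power than 15.

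**What to change.** - State one planned number of clinicians in the abstract, the study design section and the sample size section, or say what 13 denotes (for example, clinicians enrolled).
- Align the planned and analysable visit totals with that number: 375 and 300 for 15, or 325 and 260 for 13.
- If 13 is the real number, or 15 is only a maximum, restate the power or the detectable difference for that number, or for both 13 and 15. Use the authors' own ICC from the clustered power analyses they mention, and state how many visits per clinician enter the comparison.
- Do not print 0.59 as a fixed figure; it depends on assumptions made here.

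The cost is wording and one restated calculation, possibly with a less favourable figure. No extra enrolment is needed.
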